### Recruitment

One aim of the proposed study is to examine recruitment and retention to a randomised trial design and inform recruitment strategies that could be used in the development of a full-scale, multi-centre trial. Therefore, this pilot randomised trial will use a multi-point recruitment strategy, involving primary health care services, specialist intellectual disability services, relevant voluntary organisations and care provider organisations. A record will be kept of the numbers of potential participants, and individuals consenting to participate in the study, identified from each of the recruitment points.

The research team will visit staff working in these settings to explain the study and ask if their organisation would be willing to support recruitment to the study. For those staff willing to support recruitment to the study, a supply of study information packs will be provided, comprising information about the study including an invitation for potential participants to participate. Staff will be invited to distribute these packs to service users who they think would fulfil the study inclusion criteria and potentially be willing to take part. Potential participants, who reply to the invitation to the study by post using the self-addressed envelope provided, will indicate whether they would like to meet the researcher to find out more about the study. The researcher (LH) will then contact participants to arrange a visit, at a convenient location to the participant, to discuss the study. Individuals recruited to the study may live together and/or be supported by the same family or paid carers. These factors could make it difficult to randomise people to the different treatment interventions of the study and lead to some contamination between treatments and clustering of outcomes. Cluster randomisation, stratified by (and therefore analysed with adjustment for) the number of individuals within a randomised cluster, level of intellectual disabilities and presence of Down Syndrome will account for the clustering of outcomes and minimise imbalance between study groups.

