### Sample size

There is limited data from controlled trials of weight management involving adults with intellectual disabilities on which to base a sample size calculation. This study is designed to estimate recruitment and retention rates for a full-scale clinical trial; it is not powered to detect a difference between study groups. Sixty-six participants will be recruited (33 to each treatment arm). This will provide sufficient insight into recruitment and retention rates, which will have a 95% confidence interval of no more than ±10%. The sample size will allow for a possible attrition rate of 20%. This study also aims to determine likely variance of study outcomes in order to power a larger randomised trial; if 50 participants provide outcome data at 12 months, a 90% confidence interval for each variance estimate will have a width of approximately 70% of the estimate (i.e. −26% to +44%).

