After obtaining informed consent, the researcher will arrange a visit to collect baseline outcome measures. Participants’ level of intellectual disability will be assessed with questions assessing an individual’s level of ability and need for support in five key areas of functioning: eating and drinking, intimate care, personal safety, communication and decision making. A total score (range 5–25) is obtained by adding together the scores from the five individual questions. This will be used to categorise the level of intellectual disability as mild, moderate, severe or profound. The cut-offs corresponding to the four categories of intellectual disabilities were derived in a previous study [22] and shown to have a good level of agreement with a validated structured assessment of functioning and ability level, the Vineland’s Adaptive Behaviour Scale [23]. Participants will then be randomised into the TAKE 5 intervention or WWToo intervention. The researcher will telephone an interactive voice response system (IVRS), hosted by the Robertson Centre for Biostatistics, University of Glasgow. The researcher will register each participant in the study, by giving the participants’ cluster number, the number of individuals within the cluster, level of intellectual disabilities and presence of Down Syndrome. After registering each participant, the system will notify the principal investigator of the allocation (TAKE 5 intervention or WWToo intervention). During post randomisation, participants will be contacted by the research dietitian delivering the interventions and arrangements will be made for their first session. Intervention sessions will take place in a participant’s own home or, if an individual prefers, in out-patient facilities located in the local learning disabilities team base, or other NHS Greater Glasgow & Clyde setting. The researcher collecting the data will be blind to group allocation. After the first 6 months of weight loss phase and at 12 months, all outcome measures will be repeated. These data will be used to determine whether any changes in outcome measures have been maintained.

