### Data analysis

The main analysis of the pilot study will include descriptive statistics of feasibility outcomes, including recruitment rates and the acceptability of randomisation (recorded from attrition rates). This analysis will help inform the development of a full-scale trial. Additional analysis of patient-centred outcomes will be carried out according to a detailed pre-specified statistical analysis plan. The primary efficacy analysis, change in body weight at the end of the intervention period (≈12 months) from baseline will use a linear regression (random effects) model to take into account clustering and will be adjusted for randomised group, baseline weight and variables used in the minimisation algorithm (level of intellectual disabilities and presence of Down Syndrome). Similar linear regression models will be fitted for each continuous secondary outcome measure. A logistic regression model will be fitted for the categorical outcome, weight loss of 5% or more of initial body weight taking account of clustering and baseline adjustments listed above. Further analyses may assess the effects of baseline characteristics on outcomes and investigate the evidence for interactions with treatment effects using regression models.

Analyses will be conducted according to the intention to treat (ITT) principle. Per-protocol analyses, including only those participants who engaged with the programme, will also be used to test the sensitivity of the ITT results. Analyses will initially be performed using only those individuals for whom outcome data are available. Participants, who are lost to follow-up, will be assessed to see if they were different at baseline to those included in these analyses. As this is a pilot trial, the level of missing data will be recorded, but no value imputation for outcome variables will be conducted.

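### The primary and secondary models list only two of the three allocation factors: cluster size, which the article says will be adjusted for, is missing

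*Protocol article*

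**What the plan says.** Three places in the protocol article bear on this.

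- **Recruitment.** Randomisation is by cluster, "stratified by (and therefore analysed with adjustment for) the number of individuals within a randomised cluster, level of intellectual disabilities and presence of Down Syndrome". That is three factors, with an explicit commitment that the analysis adjusts for each.
- **Procedure.** The researcher registers each participant with the randomisation system by "giving the participants’ cluster number, the number of individuals within the cluster, level of intellectual disabilities and presence of Down Syndrome". The same three factors are therefore inputs to the allocation, together with the cluster identifier.
- **Data analysis.** The primary analysis of 12-month weight change "will use a linear regression (random effects) model to take into account clustering". Its covariates are randomised group, baseline weight and the "variables used in the minimisation algorithm (level of intellectual disabilities and presence of Down Syndrome"). Two allocation factors are listed and cluster size is not. The continuous secondary outcomes get similar models, and the logistic model for 5% weight loss is fitted "taking account of clustering and baseline adjustments listed above", so both inherit the shorter list.

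The allocation is called stratified in Recruitment and a minimisation algorithm in Data analysis.

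**The concern.** The two covariate lists cannot both be followed. One section promises adjustment for cluster size; the section that specifies the model leaves it out and describes the remaining two as the allocation variables.

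When allocation is balanced on a factor related to outcome, the treatment estimate varies less between repetitions of the trial than an unadjusted model assumes. Leaving the factor out then gives standard errors that are too large, intervals that are too wide and a test that rejects too rarely. Cluster size could be related to outcome: Recruitment links clusters to shared homes and shared carers, and the Interventions section says that carer involvement contributes to effectiveness. The article gives no data on how strong that relation is.

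There is also a procedural stake. With two published covariate sets, whoever analyses the trial has a choice that should be closed before outcome data are seen.

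**Working it through.** **1. The factor lists side by side**

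| Section | Cluster size | Disability level | Down syndrome | Term for the method |
|---|---|---|---|---|
| Recruitment (allocation and promised adjustment) | yes | yes | yes | stratified |
| Procedure (inputs to the randomisation system) | yes | yes | yes | none given |
| Data analysis (model covariates) | no | yes | yes | minimisation algorithm |

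**2. Does the random effect stand in for the missing covariate?** No. A random intercept for cluster allows members of one cluster to be correlated. It does not estimate a systematic difference in mean weight change between people in clusters of one and people in larger clusters. Data analysis itself treats the two as separate: the random effect handles clustering, and the covariates are listed in addition.

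**3. Do the article's own figures depend on this point?** The Sample size section states "Sixty-six participants will be recruited (33 to each treatment arm"), 20% attrition, rates estimated to within ±10%, and a 90% interval for a variance of −26% to +44% with 50 participants.

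- Variance interval with 49 degrees of freedom: 49/χ²(0.95) − 1 = −26.1% and 49/χ²(0.05) − 1 = +44.4%, a width of 70.6%. This reproduces the stated figure.
- Half-width for a 20% attrition rate: 1.96 × √(0.2 × 0.8 / 66) = 9.65%, which agrees with ±10%.
- Expected completers: 66 × 0.8 = 52.8, in line with the 50 used.

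None of these uses the covariate list, so none changes.

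**4. Size of the effect in the linear models.** Let R² be the share of outcome variance that cluster size explains beyond baseline weight, disability level and Down syndrome. The article gives no value, so the range 0 to 0.10 is an assumption. Suppose, as a simplification, that the arms are balanced on cluster size. Then:

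- ratio of reported to correct standard error = 1/√(1 − R²)
- actual type I error at nominal 5% = P(|Z| > 1.96/√(1 − R²))

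| Assumed R² | Standard error ratio | Critical value | Actual type I error |
|---|---|---|---|
| 0 | 1.000 | 1.960 | 5.0% |
| 0.05 | 1.026 | 2.011 | 4.4% |
| 0.10 | 1.054 | 2.066 | 3.9% |

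These are approximations for the linear models and do not carry over directly to the logistic model.

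**The case against.** **The commitment is already in the article, and a separate analysis plan exists.** Recruitment promises the adjustment, and Data analysis refers to a detailed pre-specified plan that is not shown. A reader might infer that the trial will certainly be analysed without cluster size. The article does not establish that; it shows two lists that differ. This limits the point to a contradiction that has to be resolved, but does not remove it, because an analysis plan cannot agree with both sections.

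**The effect may be nil.** Recruitment says only that participants may live together or share carers. If nearly all clusters are single people, cluster size hardly varies and R² is close to zero. This stands, and is why the range starts at zero.

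**The direction is conservative and the trial is a pilot.** The Sample size section says the study is not powered for a group difference, and Data analysis makes descriptive feasibility statistics the main analysis. Omission does not create false positives. This also stands.

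**A reader might infer that the full trial will be oversized.** By the same formula, 1/(1 − R²) gives 1.05 to 1.11 at R² of 0.05 to 0.10. The article does not support that consequence. It asks for the sample size of a full trial and speaks of the likely variance of outcomes, but never says that the residual variance of this model will be used. If the raw outcome variance is used, the covariate list has no bearing. Cluster size is also constant within a cluster, so in a random-effects model its unexplained contribution falls mainly in the between-cluster component, not the residual. A shift of 5–11% would in any case be small beside the article's own −26% to +44%.

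**A reader might infer a real conflict over the allocation method.** With four disability levels, two Down syndrome levels and an assumed two or three size bands, full stratification gives 16 to 24 cells, or 66/16 = 4.1 to 66/24 = 2.8 participants per cell. But the article states no bands, and Recruitment itself gives minimising imbalance as the aim. Stratified is probably used loosely for balancing factors, so this is a matter of terminology.

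**Conclusion.** The point holds as an inconsistency in the specified adjustment set. Cluster size is an allocation factor in two sections and a promised covariate in one, yet it is absent from the primary model and the secondary models built on it. That conclusion needs no assumption beyond the text.

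Its numerical effect is modest and on the conservative side: standard errors too large by 0–5.4%, and a type I error between 5% and about 3.9%. This rests on an assumed 0–10% of variance explained beyond the other covariates and on balance between the arms. No stated sample size or precision figure is affected. An inflated full-trial sample size is not established, and the difference between stratified and minimised is most likely loose wording. The correction is still worth making, because it is cheap and makes the analysis match the design.

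**What to change.** In Data analysis, add cluster size as a fixed covariate, for example one person versus two or more, to the primary model and to every secondary model, and keep the random effect for cluster. The adjustment set then equals the three factors given to the randomisation system. If the system used particular size bands, use the same ones in the model.

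Use one term for the allocation method in Recruitment and Data analysis, whichever describes what the randomisation system does. Make both changes before outcome data are analysed, and make sure the statistical analysis plan carries the same list.

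The cost is 1–2 degrees of freedom and a wording correction. Because the covariate is constant within a cluster, those degrees of freedom should be counted against the number of clusters, which the article does not give, and not against the roughly 50 participants expected at 12 months.

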## Methods

The study will be conducted in accordance with the ethical principles of the Declaration of Helsinki and consistent with the principles of Good Clinical Practice. Ethical approval has been received from the Scotland A Research Ethics committee. In accordance with the Adults with Incapacity (Scotland) Act 2000, a detailed protocol of consent was implemented. This included seeking consent from individuals with intellectual disabilities with the capacity to provide informed consent and seeking consent from the nearest relative or welfare guardian in circumstances where the individual was unable to provide informed consent. Written informed consent was obtained from all participants or nearest relative or welfare guardian. Participants will have the right to withdraw from the study at any time and to decline to take part in any particular aspect or measure. This will be explained to them whilst seeking consent and their on-going consent will be checked and assessed throughout the intervention.

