#### Anthropometric outcomes

Participants will be invited to have their weight, height, waist circumference and triceps skinfold thickness measured. Measurements will be made with the participant wearing light clothes without shoes. All measurements will be made in duplicate and the final value calculated as the mean of the two measurements. Weight in kilograms will be measured to the nearest 100 grams (g), using SECA877 scales (SE approval class III; SEA Germany). Height in metres (m) will be measured to the nearest 1 mm using the SECA Leicester stadiometer (SECA, Germany). The height (m) and weight (kg) will be used to calculate BMI using the formula BMI = weight/height (kg/m^2^).

Waist circumference will be measured to the nearest 0.5 cm at the midpoint between the iliac crest and the lowest rib, in full expiration whilst the participant is standing [34].

Due to the invasive nature of skinfold measurements and the issue of level of compliance of adults with intellectual disabilities, percentage body fat will be calculated using only the triceps skinfold thickness (mm) measured to the nearest 1 mm, waist circumference (cm) and age (years) of the participant. Separate regression equations for male and female participants, developed by Lean et al. [35] will be used to predict body density and percentage body fat.

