#### Physical activity outcome

To objectively measure physical activity, all participants will be invited to wear accelerometers for 7 days on three occasions, at baseline, 6 and 12 months. Accelerometers have been used in studies involving adults with intellectual disabilities and shown to be well utilised by this group and to be a reliable and effective measure of levels of physical activity [36, 37].

Actigraph GT3X+ accelerometers (Manufacturing Technology Inc., Florida) will be worn at the hip, attached to a belt worn round the waist. Participants will be invited to wear the actigraph GT3X+ over a 7-day period. Instructions will be given to wear the actigraph during all waking hours, except when showering, bathing or swimming.

In keeping with guidelines on the validity of accelerometer data, the minimum data requirement will be set at 6 h of data, on at least 3 days from seven [38]. If this requirement is not met, the accelerometer data will be discarded and not be included in the analysis. The number of participants who fail to record sufficient records of physical activity will be recorded. The accelerometers will be set to record activity over 15-s intervals (epochs), with activity counts of four consecutive epochs summed to give activity counts per minute (cpm). Based on recommendations from previous studies [39], four categories of activity intensity will be defined:

Sedentary behaviour 0–499 cpm.Light intensity activity 500–1,951 cpm.Moderate intensity activity 1,952–5,724 cpm.Vigorous intensity activity greater than 5,725 cpm.

The accelerometer data will then be used to calculate the mean time (minutes) and the percentage time per day, spent in each level of activity.

In addition, physical activity levels will also be measured subjectively by administering the International Physical Activity Questionnaire-Short (IPAQ-S). This will provide information about the types of physical activity they participated in.

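### For percentage body fat, and for the accelerometer outcomes if they are adjusted for their own baseline, a missing baseline removes a valid 12-month result, and attendees without usable data are counted but not compared with those analysed

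*Protocol article*

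**What the plan says.** All section names refer to the protocol article.

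- **Primary model (Data analysis).** The response is a change: "change in body weight at the end of the intervention period (≈12 months) from baseline will use a linear regression (random effects) model". The model "will be adjusted for randomised group, baseline weight and variables used in the minimisation algorithm".
- **Secondary models (Data analysis).** "Similar linear regression models will be fitted for each continuous secondary outcome measure".
- **Definition of the outcomes (Secondary outcome).** BMI, waist circumference and percentage body fat are listed as changes. The three activity outcomes (moderate-vigorous, light, sedentary) are listed in a separate sentence as mean percentage of time per day, without the word change.
- **Missing data (Data analysis).** "Analyses will initially be performed using only those individuals for whom outcome data are available". The level of missing data is to be recorded, and outcome variables are not to be imputed. The one comparison on baseline characteristics is this: "Participants, who are lost to follow-up, will be assessed to see if they were different at baseline to those included in these analyses".
- **Accelerometer rule (Physical activity outcome).** The device is worn at baseline, 6 and 12 months, and a record needs at least 6 h on at least 3 of 7 days. "If this requirement is not met, the accelerometer data will be discarded and not be included in the analysis". The number of participants with insufficient records is to be noted.
- **Skinfold (Anthropometric outcomes).** Only the triceps site is used, "Due to the invasive nature of skinfold measurements and the issue of level of compliance of adults with intellectual disabilities". Percentage body fat is computed from it.
- **Right to decline (Methods, opening paragraph).** Participants may stay in the study and still choose "to decline to take part in any particular aspect or measure".

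**The concern.** For body weight the model is harmless: Table 1 requires a BMI of at least 30, so every participant has a baseline weight. Percentage body fat and the accelerometer outcomes have no such guarantee, and the article itself foresees discarded records, difficult skinfolds and declined measures.

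Two consequences follow.

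1. A participant who attends at 12 months and gives a usable value, but whose baseline value is unusable, has no change score and no baseline covariate. An observed post-randomisation result is then lost because of a gap that arose before randomisation.
2. An attendee with a discarded record or a declined skinfold is not lost to follow-up, so the stated baseline comparison does not reach that person. A count shows how many could not supply the measure. It does not show whether they differ from the rest, for example in level of intellectual disability.

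The second matters because the Aim section asks whether the outcome measures are acceptable and can be measured reliably. The first bears on the Sample size section, which states a precision for each variance estimate on the basis of 50 participants with 12-month data.

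**Working it through.** **Inputs from the article.** 66 participants randomised; attrition 20%; 50 assumed to provide 12-month data; 90% confidence interval for a variance of −26% to +44%.

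**Inputs assumed.** The article gives no rate of usable records. Let *p* be the share usable at each visit, taken as 0.8, with 0.9 and 0.7 as the range. Let *c* be the within-person correlation of usability between visits, taken as 0 (independent) or 0.5.

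**Step 1: the article's own figure.** The interval for a variance is df/χ²(0.95, df) − 1 to df/χ²(0.05, df) − 1. With df = 49 it is −26.1% to +44.4%, a width of 70.6%. The stated figure is reproduced.

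**Step 2: who is needed.** With *B* the baseline value, *Y* the 12-month value and *T* the arm, the copied model is Y − B = α + τT + βB. It needs both *B* and *Y*. Moving *B* to the right gives Y = α + τT + (β + 1)B, so on complete pairs the treatment effect τ is identical. Changing the response alone alters nothing for people with both values. It does mean that a missing *B* becomes a missing covariate and no longer a missing outcome.

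**Step 3: expected counts.** Attendees: 66 × 0.80 = 52.8. Usable at 12 months: 52.8p. Usable at both visits: 52.8[p² + c·p(1 − p)].

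| p | c | Usable at 12 months | Usable at both | Valid 12-month values dropped |
|---|---|---|---|---|
| 0.9 | 0 | 47.5 | 42.8 | 4.8 |
| 0.8 | 0 | 42.2 | 33.8 | 8.4 |
| 0.8 | 0.5 | 42.2 | 38.0 | 4.2 |
| 0.7 | 0 | 37.0 | 25.9 | 11.1 |

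For p = 0.8 and c = 0.5: 0.64 + 0.5 × 0.16 = 0.72, and 52.8 × 0.72 = 38.0.

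**Step 4: effect on the treatment estimate.** If a person without a baseline carried full information, the variance would rise by 1/p = 1.25 at p = 0.8 and c = 0. That is an upper bound, because such a person carries less. A simulation gives the realistic figure: 53 attendees, two arms, normal data, no true effect, baseline to 12-month correlation 0.5 or 0.7, no clustering. It compares the change model on complete pairs with the 12-month value model using a pooled-mean fill and an indicator. Variance ratios (correlation 0.7 to 0.5):

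- p = 0.8, c = 0: 1.05 to 1.18
- p = 0.8, c = 0.5: 1.01 to 1.06
- p = 0.9, c = 0: 1.01 to 1.06
- p = 0.7, c = 0: 1.13 to 1.31

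Neither method showed bias. On the standard-error scale the p = 0.8 results are √1.05 to √1.18, about 2% to 9%, and √1.01 to √1.06, about 0.5% to 3%.

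**Step 5: effect on a variance estimate.** Using the Step 1 formula at p = 0.8, 33.8 pairs give −30% to +58%, 38.0 pairs give −29% to +54%, and 42.2 values give −28% to +50%. Most of the departure from −26% to +44% comes from unusable 12-month records, which no handling of the baseline can restore.

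**Step 6: reach of the baseline comparison.** It covers 66 × 0.20 = 13.2 people lost to follow-up. At p = 0.8 a further 52.8 × 0.20 = 10.6 attendees have no usable 12-month record and fall outside it.

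**The case against.** The strongest reply is that the article points to a detailed statistical analysis plan, which is not at hand, and that handling of a missing baseline covariate normally belongs there. The bar on imputation names outcome variables only, and the available-data analysis is described as what is done initially. The activity outcomes are not defined as changes, so for three of the four outcomes the need for a baseline value rests on how closely the secondary models copy the primary one.

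Much of this stands. For the activity outcomes the point is conditional on adjustment for their own baseline, and the present text would not forbid filling that covariate. For percentage body fat the reply is weaker. The outcome is a change, so filling a missing baseline fills part of the outcome, and the article rules that out unless the response is restated.

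A reader might infer that the plan ignores attendees with unusable data. It does not: insufficient accelerometer records are counted and the level of missing data is recorded. Only the comparison with those analysed is absent.

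A reader might also infer bias or a large loss. The simulation shows no bias. The article gives no failure rate, describes accelerometers as well used in this population, sets a lenient wear threshold and limits skinfolds to one site. If the same people fail at both visits, which is plausible, the number of valid results dropped at 80% usability falls from about 8 to about 4.

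**Conclusion.** The point holds in a limited form. For percentage body fat, and for the three accelerometer outcomes if their models adjust for their own baseline, the stated models discard valid 12-month values from attendees without a usable baseline. The stated baseline comparison leaves out attendees without analysable data.

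The loss is of precision and is modest. At an assumed 80% usability per visit, the variance of the treatment effect is about 5% to 18% higher under independence and about 1% to 6% higher with a within-person correlation of 0.5. These figures rest on the assumed rates, on usability being unrelated to the outcome, and on ignoring clustering.

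The documents do not support extending the point to the primary weight outcome, which has a guaranteed baseline, or to waist circumference, for which no specific gap is shown. In a pilot not powered for group differences this is a cheap improvement and not a serious flaw. Its more useful half is the wider comparison, because that answers one of the pilot's own feasibility questions.

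**What to change.** Two changes to the analysis text:

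1. For percentage body fat and the three accelerometer outcomes, make the 12-month value the response, with the baseline value as covariate. Where only the baseline is missing, set it to the mean of all participants with a baseline, both arms together, and add a missing-baseline indicator. Baseline precedes randomisation, so the fill does not favour either arm, and no outcome is imputed.
2. Replace the comparison of those lost to follow-up with a comparison of baseline characteristics, for each outcome and by arm, between all participants with and without an analysable 12-month value.

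The cost is two sentences, a few lines of code and one extra term in four models. No new data are needed. One limit remains: the first change brings every usable 12-month value into the treatment comparison and into the variance of the 12-month value, but the variance of the change, or of the outcome adjusted for baseline, still rests on complete pairs. The number behind each variance estimate should therefore be reported beside it.

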### Outcome measures

A researcher (LH) who is blind to study group allocation is responsible for collecting all outcome measures. Demographic, health questionnaires and all other outcome measures will be completed at baseline, at 6 months and at 12 months.

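### The primary weight analysis is labelled ITT but leaves out the 6-month weights already collected, so drop-out after 6 months can bias it in either direction

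*Protocol article*

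**What the plan says.** All references are to the protocol article.

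- **Primary outcome:** the difference between arms in body weight change from baseline to 12 months.
- **Data analysis, model:** a linear regression of change at about 12 months, adjusted for group, baseline weight, level of intellectual disabilities and Down Syndrome. The random effect is there for clustering. It does not link repeated visits.
- **Data analysis, analysed set:** the analyses are said to follow the ITT principle, but "Analyses will initially be performed using only those individuals for whom outcome data are available".
- **Data analysis, missing values:** "the level of missing data will be recorded, but no value imputation for outcome variables will be conducted". The reason given is that this is a pilot.
- **Data analysis, checks:** those lost to follow-up are compared at baseline with those analysed. In addition, "Per-protocol analyses, including only those participants who engaged with the programme, will also be used to test the sensitivity of the ITT results".
- **Outcome measures:** "all other outcome measures will be completed at baseline, at 6 months and at 12 months". Weight is among them. The Procedure section says the repeated measures serve to show whether changes were maintained.
- **Sample size:** 66 participants, 33 per arm. "The sample size will allow for a possible attrition rate of 20" per cent. The precision of the variance estimate is worked out on the condition that "if 50 participants provide outcome data at 12 months".

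**The concern.** The model has one response per person, at 12 months, and no term for the 6-month weight. Someone measured by the blinded researcher at 6 months and then lost is dropped from the effect estimate, although that weight is informative about the missing 12-month value. The estimate is then unbiased only if drop-out is unrelated to 12-month change given arm and baseline variables.

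Drop-out linked to the 6-month result is a reasonable thing to guard against here. Under Design, what a participant is advised to do after month 6 depends on whether 5% of initial weight has been lost by then.

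Neither stated check reaches this. A baseline comparison cannot reveal drop-out driven by weight change after baseline. A per-protocol analysis selects on engagement, which is a different question.

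The study is not powered for a group difference and feasibility is its main analysis. Even so, weight is the named primary outcome, the Aim asks for the sample size of a full trial based on body weight, and the Conclusion makes the next step depend partly on a significant effect on outcome measures.

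**Working it through.** **The plan's own figures.**
- Retention at 20% attrition, n = 66: 1.96 × √(0.2 × 0.8 / 66) = 0.0965, or ±9.65 points. The article says "which will have a 95% confidence interval of no more than ±10" per cent, which agrees.
- Variance interval with 50 completers, df = 49: 49/χ²(0.95) − 1 = −26.1% and 49/χ²(0.05) − 1 = +44.4%. The stated −26% to +44% is reproduced.
- 20% attrition leaves 66 × 0.8 = 52.8 participants. The 50 completers would mean 16/66 = 24% lost.

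The article gives no effect size or SD for weight change, so the rest uses assumed inputs.

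**Formula.** Let β = ρ × SD12/SD6 be the slope of 12-month on 6-month change. Let δ be, in each arm, the mean 6-month change of those seen at 12 months minus that of the whole arm. When drop-out depends on 6-month change, the available-case bias is β × (δ in TAKE 5 − δ in control).

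**Assumed inputs.** True difference −3 kg at both visits (negative favours TAKE 5); SD6 = 5 kg and SD12 = 7 kg; ρ = 0.60, 0.75, 0.85; 6% lost at random before 6 months and 20% lost in total in each arm. Where drop-out depends on 6-month change, the log-odds rise by 0.30 per kg of poorer change relative to the arm mean. In simulation this gives δ ≈ −0.87 kg in an affected arm.

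- β = 0.60 × 7/5 = 0.84; 0.75 × 7/5 = 1.05; 0.85 × 7/5 = 1.19.
- Bias if only TAKE 5 is affected: −0.87 × 0.84 = −0.73 kg; −0.87 × 1.05 = −0.91 kg; −0.87 × 1.19 = −1.04 kg (benefit overstated).
- Bias if only control is affected: the same sizes with the opposite sign (benefit understated).

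Large-sample simulation of three estimators (bias in kg over the three values of ρ):

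| Drop-out after 6 months | Available-case | Repeated measures, unstructured | Repeated measures, participant random intercept only |
|---|---|---|---|
| Completely random | 0 | 0 | 0 |
| Same in both arms, relative to arm mean | 0 | 0 | 0 |
| TAKE 5 only | −0.73 to −1.04 | 0 | −0.25 to −0.35 |
| Control only | +0.72 to +1.04 | 0 | +0.24 to +0.35 |

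Zero here means within 0.02 kg. The random-intercept model forces equal variances at 6 and 12 months, so it uses the wrong slope and leaves about a third of the bias (0.25/0.73 = 34%).

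**Other assumed inputs.** SDs 4.5 and 6 kg, ρ 0.6 to 0.8, 20% lost, half or all of it after 6 months, and drop-out depending on absolute rather than arm-relative 6-month change:
- poorer change raises drop-out in both arms: +0.3 to +0.5 kg at 0.3 per kg, +0.5 to +0.9 kg at 0.6 per kg;
- TAKE 5 only, 0.3 per kg: −0.4 to −1.0 kg;
- control only, 0.5 per kg: +0.9 to +1.9 kg;
- opposite directions in the two arms: −0.9 to −2.1 kg;
- repeated-measures estimate in every case: at most about 0.03 kg.

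**Against sampling error.** With 33 × 0.8 = 26.4 per arm, SE = 7 × √(2/26.4) = 1.93 kg, or 6 × √(2/26.4) = 1.65 kg with the smaller SD. Simulated values run from about 1.5 to 1.9 kg, with little difference between methods. All of this ignores clustering and the randomisation factors.

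**The case against.** **The detail belongs to the analysis plan.** The article defers patient-centred outcomes to a detailed plan that is not shown, and the word *initially* leaves room for more. But the article itself fixes the model, the analysed set, the imputation rule and the checks, and names no further analysis for missing outcomes. The point is about a stated method, so this does not remove it.

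**The bias is conditional.** This stands. A reader might infer that the analysis will exaggerate TAKE 5 because people who do not lose weight leave. The documents give no evidence on who leaves, and the control arm gets the same number of one-to-one sessions. Depending on the mechanism, the bias is zero, favours TAKE 5 or works against it.

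**The 6-month weights are not thrown away.** Also correct. They are used to describe maintenance and are absent only from the 12-month model.

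**The per-protocol analysis never claims to test missing data.** Correct. It is offered as a sensitivity analysis for the ITT result. The fair criticism is only that nothing stated covers post-baseline drop-out.

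**The variance estimates are hardly touched.** A reader might infer that the variance carried to the full trial is seriously distorted. In a check with slope 0.30, the TAKE 5 variance fell from 49 to 44–46, a fall of 6–10% in one arm and so roughly 3–5% pooled. That is small beside the plan's own −26% to +44%.

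**This is a pilot, and the bias is below the SE.** True for most settings, and it limits the severity. It may justify not imputing, but it gives no reason to leave out weights already observed.

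**Conclusion.** The point holds in a limited form. An analysis called ITT uses only those weighed at 12 months and ignores 6-month weights that are in hand. If drop-out after 6 months depends on 6-month change differently by arm, the estimate can be off by roughly 1 kg in either direction, on an assumed −3 kg effect with SDs of 5 and 7 kg and 20% attrition. The wider assumed settings span about 0.3 to 2.1 kg. Under random drop-out, or the same arm-relative mechanism in both arms, there is no bias.

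The 20% is an allowance, not a forecast, and no source in the article fixes the effect, the SDs, the correlation or the drop-out mechanism. The sampling SE of about 1.5 to 1.9 kg exceeds most of these biases. The change is still worth making: it rests on a weaker missing-data assumption, needs no new data, and the result may feed the decision on a full trial.

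**What to change.** Make the primary weight model a likelihood-based repeated-measures model on change at 6 and 12 months. Terms: visit, group, group-by-visit, baseline weight by visit and the randomisation factors, with a cluster random effect. Specify an unstructured within-participant covariance, which needs only three parameters for two visits. A participant random intercept alone is not enough. Report the 12-month contrast as the primary result. Everyone with at least one follow-up weight is included, and the no-imputation rule is kept.

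Keep the 12-month available-case regression as a sensitivity analysis. State that the per-protocol analysis addresses engagement, not missing outcomes. Use the same model form for the continuous secondary outcomes.

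The cost is a change of wording and slightly more programming. The model relies on data being missing at random given the observed weights, and it does nothing for participants lost before 6 months, whose number should be reported by arm.
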